#### Primary analyses

##### Main outcome 18F-DOPA

State-of-the-art image processing will be used to analyze PET and fMRI images. PET image pre-processing and analysis will be done using PMOD (PMOD software, PMOD technologies Zurich) and SPM (Wellcome Department of Imaging Neuroscience, London, UK) for the 18F-DOPA study. The most often used method to quantify biochemical function from 18F-DOPA PET image is the multiple time graphical approach (MTGA) that provides rate constants (Ki) for the storage of 18F-DOPA within regions of interest (ROIs) placed over the striatum [8] and in regions associated with the processing of reward. Images from each dynamic DOPA PET dataset will be aligned and parametric images of 18F-DOPA influx (Ki) will be created for each subject. The Ki images will be transformed into standard stereotactic space. Regional Ki values of striatal regions (putamen, caudate, nucleus accumbens) will be analyzed with statistical parametric mapping for comparison of regional Ki values on a voxel by voxel basis. Group comparisons will be tested using independent samples *T*-test for pre-test measures; treatment group × time comparisons will be analyzed with two-factorial ANOVA’s including Ki values obtained in the nucleus accumbens and the caudate to test the primary outcomes. Regional Ki values can be reported into SPSS for the main analyses and for associations with the other data. Exploratory analyses can include additional moderation and mediation analyses on the basis of the results.

##### Main outcome: questionnaire measuring pain: VRS and BPI scores

The analyses for the VRS and BPI scores will be performed with a two-factorial (treatment group × time) ANOVA. In case of not normally distributed data, we will use a transformation in Z-scores, rather than using non-parametric tests. Pre-test comparisons with healthy controls will be performed with *T*-tests.

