#### Main primary outcome

1) A.18F-DOPA influx: the difference between FM patients and healthy controls at pre-test and between pre-test and post-test in FM

1) B. Measures of pain symptoms: the difference between FM patients and healthy controls at pre-test and between pre-test and post-test in FM in the scores of the 1-item Verbal Rating Scale (VRS) [70] and of the Brief Pain Inventory (BPI) [15].

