• In order to have a sample size sufficient to obtain significant results for the primary outcomes (FDOPA) and clinical pain measures as well as for the secondary outcomes (in particular daily life measures), we consider a minimal sample of *N* = 20 in each FMS group. Considering a 20% drop-out in total yields to a starting sample of 25 participants in each FMS group (MORE and non-intervention control). To account for data loss related to technical problems as well as for the average size of the MORE group of *N* = 8, we will round up to *N* = 32 in each FMS group.

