### Questionnaires

#### Pain-related outcomes

• *Pain severity and functional interference*: The Brief Pain Inventory (BPI) is used to obtain information on self-reported measures of pain severity and functional interference using the BPI [15]. Pain magnitude is queried by four items that ask about pain now, worst pain, least pain, and average pain. Items use numeric rating scales anchored by 0 (no pain) to 10 (most severe pain). Pain interference consists of seven items that ask about how pain interferes with aspects of daily living using numeric rating scales anchored by 0 (no interference) to 10 (completely interferes).

• *Current pain intensity*: The 1-item Verbal Rating Scale (VRS) from the SF-36 [70] is used to measure current pain intensity. The VRS has proven itself over decades as a valid, reliable, and change-sensitive measure of subjective pain [70].

• *Pain interference with functional impairment*: To measure the degree to which pain interferes with function in major life areas, we will use the 7-item Pain Disability Index (PDI) [18].

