
##### Secondary outcome: clinical and FM pain-related symptoms

The analyses of the measures related to the clinical and FM pain-related symptoms including measures of pain intensity and severity, functioning, sleep, mood, and quality of life will be analyzed with a two-factorial (treatment group × time) ANOVA. In case of not normally distributed data, we will use a transformation in *Z*-scores, rather than using non-parametric tests. Pre-test comparisons with healthy controls will be performed with *T-*tests. For the analyses of the effects at follow-up, we will add an additional level to the time factor (pre-test, post-test, and follow-up). Exploratory analyses can include additional moderation and mediation analyses on the basis of the results.

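### The stated remedy for non-normal pain and clinical scores, a Z-score transformation, is a linear rescaling and does nothing about non-normality

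*Protocol article*

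**What the plan says.** The protocol article, under the heading for the main outcome on questionnaire pain measures, sets the analysis: "The analyses for the VRS and BPI scores will be performed with a two-factorial (treatment group × time) ANOVA". It then gives the rule for departures from normality: "In case of not normally distributed data, we will use a transformation in Z-scores, rather than using non-parametric tests". Healthy controls are compared with FM patients at pre-test by t-test.

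The section on clinical and FM pain-related symptoms repeats the rule for pain, functioning, sleep, mood and quality of life, again choosing Z-scores "rather than using non-parametric tests".

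Under Main primary outcome, the VRS and BPI form item 1B: "1) B. Measures of pain symptoms: the difference between FM patients and healthy controls at pre-test and between pre-test and post-test in FM". The Abstract instead places clinical pain measures among the secondary outcomes. The rule covers them under either label.

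The article gives no other remedy for non-normality in these outcomes. It does not say which mean and SD would be used, and it describes no rank-based or other non-linear step. The r-to-z step in the fMRI section concerns correlation coefficients and is a different procedure.

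**The concern.** A remedy for non-normality has to change the shape of the distribution or change the inference so that shape matters less. A Z-score in its ordinary sense does neither. If the rule were triggered, the report could say that non-normality had been handled when nothing had changed, and the same sentence sets aside the rank-based methods that would have responded to it.

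The trigger could plausibly be met. The VRS is a single item. The BPI is built from bounded ratings ("Items use numeric rating scales anchored by 0 (no pain) to 10 (most severe pain"). Healthy controls are selected for having no history of chronic pain, so scores at the floor are plausible in the pre-test comparisons.

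The missing detail on how to standardise also matters. Some versions of a Z-score do alter the test, and the choice between versions would be open at analysis.

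**Working it through.** The protocol attaches no figure to this rule, so there is none to reproduce.

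**Inputs**
- Model: group × time ANOVA with two groups and two times (Statistical methods).
- Arm size: 32, from Sample size, where 20 evaluable with 20% drop-out gives 20 / 0.8 = 25, then rounded up to 32.
- Healthy controls: 20 (PET comparison group).
- Assumption: right-skewed, gamma-based simulated scores. The algebra below does not depend on it.

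**One mean m and one SD s for all observations**
- z = (x − m)/s with s > 0 is linear and increasing. Ranks and ties are preserved. Skewness, kurtosis and the Shapiro-Wilk W do not change under shift and scale.
- Every sum of squares is divided by s², so F = (SS_effect/df₁)/(SS_error/df₂) is unchanged. The same holds for t and p.

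| One simulated data set, 32 per arm | Raw | Pooled Z |
|---|---|---|
| Skewness | 0.78964 | 0.78964 |
| Shapiro-Wilk W (p) | 0.95516 (0.00032) | 0.95516 (0.00032) |
| Interaction F (p) | 5.291871 (0.024803) | 5.291871 (0.024803) |
| Time F | 13.514364 | 13.514364 |
| t, FM (64) v healthy (20) | 6.9936 | 6.9936 |

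Over 5,000 repeats the largest raw-versus-pooled difference in any F or p from the ANOVA was about 2 × 10⁻¹⁴, which is rounding error. Standardising on the baseline mean and SD gave the same ANOVA results.

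**Standardising within each time point**
- Each time point then has mean zero, so with equal arms the time effect is F = 0.
- Write Δ for MORE minus control. The raw interaction contrast is Δpost − Δpre. It becomes Δpost/s₂ − Δpre/s₁, a different contrast unless the two SDs are equal.
- In the same data set the interaction moved from p = 0.0248 to p = 0.0195. Significance at 5% flipped in about 4% of repeats.
- The shape at each time point did not change (post-test skewness 0.69063 both ways).

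**Standardising within each group-by-time cell**
- All four cell means are zero, so the group, time and interaction effects are all F = 0. The treatment effect is erased.

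**Contrast: a step that does change shape**
- Rank-based normal scores on the same data moved skewness from 0.79 to 0.00 and W from 0.955 to 0.9995. The interaction moved from F = 5.29, p = 0.0248 to F = 5.98, p = 0.0174. This is illustrative only.

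**Does the planned ANOVA suffer without a remedy?**
- The 2 × 2 interaction F is the square of the t-test on change, and under the null differencing removes most of the skew.
- A null simulation used 40,000 repeats, with exponential scores (skewness 2.0), a skewed 6-category item and floored 0–10 scores, at 20, 25 and 32 per arm. The pre–post correlation was about 0.5 on the latent normal scale. These distributions and the correlation are assumptions.
- Type I error at nominal 5% was 4.8% to 5.1% in all nine cases. Power and the healthy-control t-tests were not covered.

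**The case against.** The best defence is that an inert rule is harmless. With a pooled Z-score the trial simply reports the group × time ANOVA it already specifies. The null simulation gives no sign that this test loses control of its error rate at these sizes, and preferring a parametric factorial analysis to non-parametric tests is a legitimate choice. The rule is also conditional, and it does not touch 18F-DOPA, the ambulatory assessments or the saliva measures. All of that stands, and it limits the seriousness of the point.

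It does not rescue the sentence. The protocol offers Z-scoring as its answer to non-normality, and it is not one.

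Three stronger readings are tempting and are not supported:
- *The planned group × time test is invalid.* Nothing in the protocol shows this, and the check above points the other way.
- *Scores will be standardised by time point or by cell, so the treatment test will be distorted.* The article does not say how standardisation will be done, so this harm is conditional.
- *Non-normality of the VRS is nearly certain.* The article describes it as one item but gives neither its categories nor an expected distribution.

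Conversely, a charitable reader might take the phrase to mean rank-based normal scores. Those would change the shape, but the text does not say so.

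**Conclusion.** The rule is wrong as written, for a main pain outcome and for the secondary clinical scores. That no test result changes is exact when one mean and one SD are used for all observations in a test. The finer standardisations also fail to normalise, and they alter or erase the effect being tested.

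The size is limited. The consequence for the group × time comparison is probably modest at about 32 per arm. This rests on the assumed distributions in the null simulation and concerns type I error only. The pre-test comparisons with healthy controls remain unassessed, and floor scores are most plausible there. This is a should-fix correction to make before analysis. It is not evidence that the trial's main comparison is unsound.

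**What to change.** - Delete the Z-score sentence in both sections.
- Keep the planned group × time ANOVA on the raw scale.
- Prespecify a method that does respond to non-normality, for example a permutation or bootstrap p-value and interval for the interaction.
- Add a rank-based or ordinal sensitivity analysis for the one-item VRS.
- Add a rank-based or permutation check for the pre-test comparisons with healthy controls.

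The cost is one sentence in each of two sections and a little extra analysis work. No additional data or participants are needed. If the change is made before results are seen, it cannot look data-driven.

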#### Secondary analyses

##### Secondary outcome: neural responses to reward

The reward task will be performed in the fMRI scanner, and we will correlate the 18F-DOPA influx with the striatal activation obtained with the fMRI task. In order to measure the behavioral differences in the fMRI task results, in the ambulatory assessment data, and in the intervention program’s efficacy between the groups tested, we plan to use different kinds of variance analyses and multilevel analysis. The number of participants for each part of the study has been determined in order to assure a good statistical power according with this specific research domain (e.g., including potential dropout, outliers). fMRI data analysis will be performed with state-of-the art software freely available online. T1-weighted scans will be analyzed with regard to cortical thickness and subcortical volumes using surface-based morphometry implemented in FreeSurfer software suite 5.0.1 (http://surfer.nmr.mgh.harvard.edu). This includes a fully automated method. Briefly, this processing includes (1) motion correction, (2) removal of non-brain tissue, (3) automated Talairach transformation, (4) segmentation of the subcortical white matter and deep gray matter volumetric structures (amygdala, hippocampus, thalamus, caudate, putamen, pallidum, nucleus accumbens, ventricles), (5) intensity normalization, (6) tessellation of the gray matter/white matter boundary, (7) automated topology correction, and (8) surface deformation following intensity gradients to optimally place the gray/white and gray/cerebrospinal fluid borders at the location where the greatest shift in intensity defines the transition to the other tissue class. Freesurfer morphometric procedures have been demonstrated to show good test-retest reliability across scanner manufacturers and across field strengths. Obtained subcortical volumes will be normalized by individual intra-cranial volumes for further statistical analysis. Exploratory approaches will involve a vertex-based analysis across the whole brain. Diffusion MRI scans will be analyzed for structural connectivity with FMRIB software library 4.1.9 (FSL, http://fmrib.ox.ac.uk/fsl). Functional MRI scans will be analyzed for activity and functional connectivity with the latest version of Statistical Parametric Mapping (SPM, http://www.fil.ion.ucl.ac.uk/spm). Functional MRI data will be pre-processed according to the following steps: (1) slice timing correction, (2) realignment, (3) linear and non-linear normalization onto a standard EPI template, (4) voxel re-sampling to 2×2×2 mm^3^, (5) smoothing with a Gaussian kernel of 6 mm full width at half maximum, (6) detrending, (7) filtering (such that frequencies 0.01 < *f* < 0.08 Hz passed the filter), and (8) regressing out the variance of nuisance covariates. With REST toolbox 1.6, for each subject and each specified region of interest (atlas-based specification), mean signal time courses will be extracted and cross-correlated. Next, correlations will be *r*-to-*z* transformed for group-level statistics. These *z*-values can be used for comparisons across (cross-sectional) and within (longitudinal) groups or for parametric correlations with psychometric measures. A region-of-interest approach will be used in subcortical regions involved in reward to obtain beta-weights (parameter estimates) that can be correlated with the 18-FDOPA estimate parameters as well as with AA self-report means and other outcomes.

##### Secondary outcome: clinical and FM pain-related symptoms

The analyses of the measures related to the clinical and FM pain-related symptoms including measures of pain intensity and severity, functioning, sleep, mood, and quality of life will be analyzed with a two-factorial (treatment group × time) ANOVA. In case of not normally distributed data, we will use a transformation in *Z*-scores, rather than using non-parametric tests. Pre-test comparisons with healthy controls will be performed with *T-*tests. For the analyses of the effects at follow-up, we will add an additional level to the time factor (pre-test, post-test, and follow-up). Exploratory analyses can include additional moderation and mediation analyses on the basis of the results.

##### Secondary outcome: daily affect, reward, stress, and pain experience

The AA measures yield intensive longitudinal data that are clustered, as they represent series of measurements that stem from different individuals. A multilevel approach to analyze these data takes into account clustering and can therefore accommodate these data and provides flexible tools to investigate within-subject phenomena, such as responses to stressors or rewarding experiences (see [9]). Data will be analyzed with a software that allows for the simultaneous modeling of within-subject and between-subject aspects of the data, and the examination of associations among individual difference variables, and individual differences in within-subject parameters (e.g., Mplus 7.3 (Muthen & Muthen, [55]-2012) or HLM software). To correlate these measures with the 18FDOPA uptake values, mean values for the AA measures will be computed.

##### Biological outcomes

Regarding the saliva samples, we will compute the cortisol awakening response (CAR) and alpha-amylase awakening response as well as daily profiles using an area under the curve approach. The CAR resp. AA awakening and the daily profiles will be used as biological indexes of stress reactivity in everyday life. The outcome is the difference between pre-test and post-test and the comparison between the MORE group and the waitlist group.

### Safety analysis

Safety analysis includes the report and observation of potential side-effects of the MORE intervention. Should side-effects occur, we will analyze the characteristics of the participants concerned.

### Interim analyses {21b}

Interim analyses will include pre-test comparisons (healthy controls versus FM) on the main and secondary outcomes after completion of the first MORE group as well as exploratory pre-post comparisons on the main outcomes to control whether methodological adjustments have to be made. Data of the pre-test comparisons (healthy controls versus FM) after completion of the second MORE group will be used for first data presentation and if possible publication of pilot data.

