### Participant timeline {13}

The overall study duration is 4 years from June 2021 to June 2025. Recruitment will take place during the entire study duration as we will perform 4 successive groups of the MORE intervention. The study duration per participant will be between 6 and 8 months, depending on scanner availability for the pre- and post-test measures. As soon as we have a minimum of 10 FM participants (minimum 5 participants and maximum 10 participants per MORE group), we will start with the first MORE group. The first measures will ideally be performed on healthy participants. The FM participants will be randomized after screening, and the ones assigned to the MORE intervention will undergo the pre-test measures of FM first. We plan 4 to 5 weeks to perform the pre-test measures for the participants allocated to the MORE group (2 participants per week). The first MORE will take place in the center where we will have first recruited the necessary number of participants. During the duration of the first MORE group (8 weeks), we will make the pre-test measures for the non-intervention control group and begin the pre-test measures for the second MORE group. This will allow us to begin with the second group as quickly as possible after the completion of the first group. During the second MORE group, we will perform the post-test measures for the first MORE group participants and test the non-intervention controls of the second MORE group. During fall 2021, we will test participants of the healthy control group and recruit the participants for the next two MORE groups that will take place in winter/spring 2022, according to a similar schedule for the first 2 groups. In parallel, we will perform the follow-up measures for MORE 1 and MORE 2. FM participants allocated to the non-intervention group will have the possibility to participate in a MORE group at the earliest after all participants of the group have completed follow-up measures, i.e., around 20 weeks after pre-test-measures (8 weeks delay for post-test measures + 12 weeks after post-test measures). In the years 2023 and 2024, we will complete the measures for the control group as well as the follow-up measures for the FM groups.

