## Assignment of interventions: blinding

### Who will be blinded {17a}

Because there is no active control group or no placebo intervention in this study, the study staff and the participants will be unblinded.

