#### PET data acquisition

PET images will be acquired at the Department of Nuclear Medicine at the University Hospital Zurich. MRI overlay images will be acquired at 3 Tesla at the Department of Nuclear Medicine at the University Hospital Zurich, using T1-weighted sequence (MP-RAGE) to provide an anatomical framework for image analysis. 18F-DOPA is a well-validated measure of presynaptic DA function [45], and previous studies showed differences in 18F-DOPA binding between FM and healthy participants at rest [74, 75]. Subjects will have an intravenous catheter placed in their forearms. One hour before scanning, they will receive as routinely an oral dose of carbidopa 100 mg, a peripheral DOPA decarboxylase blocker and entacopone 400 mg, a peripheral catechol O-methyltransferase antagonist, and an additional 50 mg dose of carbidopa 30 min before 18F-DOPA injection in order to provide increased availability of 18F-DOPA for striatal uptake. The purpose of the premedication regimen is to limit the metabolism of the 18F-DOPA tracer by peripheral enzymes, i.e., DOPA decarboxylase and catechol O-methyltransferase, thereby maximizing central uptake [54]. Subjects will lay quietly before administration of the tracer to allow them to habituate into the environment and to relax. Subjects will then be injected with approximately 100 MBq of 18F-DOPA. Dynamic scanning will be performed up to 100 min after injection of tracer, but at least between 40 and 90 min after injection (cite https://www.ncbi.nlm.nih.gov/pmc/articles/PMC5584692/). Scans will be acquired on a PET/CT Discovery 690 scanner. Subjects will undergo the PET and MRI measures on the same day at the same place. Participants will have time to rest and to have lunch between both measures. PET measures will take place at pre-test and post-test. Pre-test measures take place 6 weeks to 1 day before the beginning of the MORE intervention. Post-test measures take place from 1 day after completion of the MORE intervention (i.e., + 8 weeks and 1 day after the beginning of the MORE intervention) to 6 weeks after completion of the MORE intervention (i.e., + 14 weeks after the beginning of the MORE intervention).

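### An early unblinded look at main-outcome changes may decide method changes that are then tested partly on the same women

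*Protocol article*

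**What the plan says.** Protocol article, Interim analyses {21b}, plans comparisons of patients with healthy women and, beyond these, "exploratory pre-post comparisons on the main outcomes to control whether methodological adjustments have to be made". The timing words stand in the string "after completion of the first MORE group as well as exploratory pre-post comparisons on the main outcomes". The section also says that the pre-test data of patients and healthy women "after completion of the second MORE group will be used for first data presentation and if possible publication of pilot data".

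Other sections set the conditions for this look:

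- **Blinding.** Who will be blinded {17a}: "the study staff and the participants will be unblinded".
- **MORE arm timing.** Participant timeline {13}: "During the second MORE group, we will perform the post-test measures for the first MORE group participants". PET data acquisition: "Post-test measures take place from 1 day after completion of the MORE intervention". The same section closes that window 6 weeks after completion.
- **Control arm timing.** Participant timeline {13}: "During the duration of the first MORE group (8 weeks), we will make the pre-test measures for the non-intervention control group". Trial design {8} puts the control post-test about 8 weeks after the pre-test.
- **Final analysis set.** The missing-data section {20c} keeps everyone with pre-test data under intention to treat. The Discussion adds a complete-data analysis. Neither leaves out the first group.
- **Main outcomes.** Outcomes {12} lists 18F-DOPA influx (1A) and the VRS and BPI pain scores (1B). Primary analyses names accumbens and caudate Ki for the primary test, alongside putamen and a voxel-wise analysis.

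**The concern.** The stated purpose of the look is "to control whether methodological adjustments have to be made", and what is looked at is the change in the main outcomes. That makes observed outcome differences the input to a decision about method. The people who decide know the allocation, and the women whose data inform the decision appear to remain in the final test. A choice of region, scale or processing step that happens to suit the first group then starts the final test with part of that chance advantage already in it.

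What is at stake is the type I error and the credibility of the final group-by-time tests. A later analysis plan could not undo this, because by then the method would already have been chosen with outcomes by arm in view.

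**Working it through.** **Base figures.** The plan gives no number for the interim look, so there is no interim figure to reproduce. The arm size used below does reproduce: 20 evaluable / (1 - 0.20) = 25 per arm, as stated in Sample size {14}, which the plan then rounds up to 32.

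**Step 1: when could the look happen?** Count weeks from the start of MORE group 1.

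- Group 1 completes at week 8.
- MORE post-test scans run from week 8 plus 1 day to week 14 (8 + 6).
- Control pre-tests fall in weeks 0 to 8. Adding about 8 weeks puts their post-tests at about weeks 8 to 16, that is 0 to 8 weeks after completion.

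A look before about week 16 may therefore have MORE-arm changes with incomplete control changes. From about week 16 it could be a complete two-arm comparison. The plan does not say which.

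**Step 2: how much could the look show?** Participant timeline {13} gives 5 to 10 women per MORE group, and Sample size {14} gives an average of 8. Assume equal numbers of controls, equal variances and no drop-out. In units of the SD of change, the 95% half-width is t(0.975, 2n - 2) × sqrt(2/n):

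- n = 5: 2.306 × 0.632 = 1.46 SD
- n = 8: 2.145 × 0.500 = 1.07 SD
- n = 10: 2.101 × 0.447 = 0.94 SD

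For d = 0.5, the pain effect cited in Sample size {14}, power at these sizes is about 11%, 15% and 19%. Missing control post-tests would widen the intervals further.

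**Step 3: what could selection do to the final test?** Assume a two-sided 5% test (the article states no alpha), 32 per arm at the end, and first-group data kept. The information fraction at the look is t = n/32: 0.156, 0.25 and 0.313 for n = 5, 8 and 10. For each analysis variant, Z_final = sqrt(t) × Z_interim + sqrt(1 - t) × Z_later. By simulation under no effect, pick the variant with the largest absolute interim statistic and test only that one at the end. Correlation between variants ranges over 0 to 0.8.

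- 8 per arm, 2 variants (for example two regions): 0.060 to 0.067
- 8 per arm, 4 variants: 0.072 to 0.091
- All cases, 5 to 10 per arm and 2 to 4 variants: 0.057 to 0.101

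If the choice instead follows the most favourable direction, the total two-sided error moves less (0.049 to 0.069). However, false positives in favour of MORE, nominally 0.025, become 0.031 to 0.067.

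If method changes were made without sight of outcome differences, or if first-group women were left out of the confirmatory test, this selection would add nothing and the error would stay at 0.05.

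**The case against.** The strongest reply has four parts.

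1. **The look is called exploratory.** No stopping rule or efficacy claim hangs on it. This stands against one stronger reading. A reader might infer that a significant early result counts as success, which would give an error of 0.089 to 0.093 with tests at 5% on 5 to 10 and then 32 per arm. The protocol contains no such rule, so that rate does not apply. The label does not answer the present point, because the declared use is to decide on method.

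2. **Safeguards exist or may exist.** The article names the regions and the ANOVA, substantial amendments need ethics approval, and the full protocol may say who decides and what may change. That is fair as to detail. Ethics approval does not control statistical error, though, and the rule linking outcome comparisons to method changes is in the text itself.

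3. **The timing is uncertain.** A reader might infer from the timeline that no post-test data exist when the look is made. The documents do not support that: completion is given as a starting point and not as a date, and post-tests open 1 day later. The timing words may even belong only to the comparison with healthy women. What remains is that the look is undated and could be partly uncontrolled.

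4. **The early comparison with healthy women is a non-randomised baseline contrast.** It reveals no treatment effect. This stands. A reader might add that testing outcome 1A repeatedly raises its error: 7.1% for 32 versus 20 followed by 64 versus 20, and 9.2% to 10.1% with an earlier look at 16 versus 20 or 16 versus 10. Those rates assume 5% at each look and group sizes that the plan does not give. Early publication of these data is a trade-off and need not be barred.

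**Conclusion.** The point holds in a limited form. The article lets changes in the main outcomes, seen by unblinded staff in roughly the first quarter of the MORE arm (8 of 32), decide on unspecified method changes. It states no protection for the final test. That the same women stay in that test is inferred from the analysis-set rule and the absence of any exclusion.

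The possible inflation is modest: about 0.06 to 0.10 instead of 0.05. It rests on an assumed alpha, 2 to 4 candidate variants and selection by size of the early difference. The case for change is clear nonetheless, because a comparison with a half-width of 0.94 to 1.46 SD gives almost no sound basis for adjusting anything. It should be corrected, but it does not invalidate the design.

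**What to change.** In Interim analyses {21b}:

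- Replace the pre-post comparison of main outcomes with a review of process measures pooled over arms: scan completion, motion, timing compliance, missing diary and saliva data, and pooled Ki variance.
- State that any method change is recorded, with date and reason, before outcomes by arm are seen.
- If baseline data of patients and healthy women are presented after the second group, label them interim and descriptive, and keep the confirmatory outcome 1A test for the full baseline sample.

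This changes wording only and keeps the technical check that the look seems meant to provide. The cost is that the early pre-post look is lost and the pilot report carries no tests.
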